## Abstract

Colorectal cancer (CRC) screening programs have been implemented to reduce the burden of the disease. When an advanced colonic lesion is detected, clinical practice guidelines recommend endoscopic surveillance with different intervals between explorations. Endoscopic surveillance is producing a considerable increase in the number of colonoscopies, with a limited effect on the CRC incidence. Instead, participation in CRC screening programs based on the fecal immunochemical test (FIT) could be a non-inferior alternative to endoscopic surveillance to reduce 10-year CRC incidence. Based on this hypothesis, we have designed a multicenter and randomized clinical trial within the Spanish population CRC screening programs to compare FIT surveillance with endoscopic surveillance. We will include individuals aged from 50 to 65 years with complete colonoscopy and advanced lesions resected within the CRC screening programs. Patients will be randomly allocated to perform an annual FIT and colonoscopy if fecal hemoglobin concentration is ≥10 µg/g, or to perform endoscopic surveillance. On the basis of the non-superior CRC incidence, we will recruit 1894 patients in each arm. The main endpoint is 10-year CRC incidence and the secondary endpoints are diagnostic yield, participation, adverse effects, mortality and cost-effectiveness. Our results may modify the clinical practice after advanced colonic resection in CRC screening programs.

## 1. Introduction

Colorectal cancer (CRC) is one of the most common malignancies in western countries. About 40,000 new cases of CRC are diagnosed each year in Spain, and 39% of those affected die due to this disease [1,2,3]. CRC screening programs have been implemented in order to reduce the burden of the disease. Screening programs are used to detect the CRC in initial stages. Furthermore, during the colonoscopy, CRC screening programs try to identify and resect the precursor lesion of the disease: the colorectal adenoma and the serrated lesions [4]. In this way, screening programs achieve a 30% reduction in the CRC incidence and a 50% reduction in CRC mortality [5].

Screening programs in Spain are based on the biennial detection of fecal hemoglobin (f-Hb) with a fecal immunochemical test (FIT) and a colonoscopy if f-Hb ≥ 20 µg/g of feces [6]. Depending on the characteristics of the resected colonic lesions, patients are classified into two different groups [7]. A low-risk group is defined when 1–2 adenomas are detected (<10 mm, tubular histology and low-grade dysplasia). On the contrary, a high-risk group is defined when at least one advanced adenoma (≥10 mm, villous histology and high grade displasia) or one serrated lesion (≥10 mm and displasia) is detected [8,9,10]. Clinical practice guidelines (CPG) have taken these characteristics into account when determining surveillance recommendations and intervals [3,8,9,10]. Patients with low-risk lesions have been routinely recommended to return to population screening programs, whereas patients with high-risk lesions are recommended to perform endoscopic surveillance with different intervals between explorations [9,11,12]. The implementation of this CRC screening strategy is producing a considerable increase in the number of colonoscopies, with a significant cost to the health system, and consuming a high proportion of the colonoscopy capacity [6]. The rate of progression of advanced adenoma to CRC is estimated to be low (2.6% in population aged 50 to 59 years and 5.6% in the population ≥80 years). Remarkably, endoscopic surveillance reduces CRC mortality by only 1.7% and increase the number of colonoscopies by 62% [13]. Moreover, colonoscopy is a procedure associated with serious side effects [4].

A recently conducted British study has evaluated the FIT diagnostic yield for CRC and advanced adenomas detection after resection of advanced lesions. With a highly sensitive cut-off (10 µg/g of feces), the sensitivity and specificity for CRC was 84.6% and 70.8% respectively, with a significant cost reduction (£2633 vs. £956 per patient) [14]. Furthermore, other studies show that the British population prefer to perform non-invasive fecal test rather than colonoscopy (60.8% vs. 31%) [15]. Based on this evidence, we have designed a randomized clinical trial within the population CRC screening programs, comparing FIT surveillance to endoscopic surveillance in patients after advanced lesion resection.

## 2. Materials and Methods

### 2.1. Hypothesis

After the resection of high-risk adenomas detected within the CRC screening program, the 10-year CRC incidence in patients participating in a CRC screening programs based on annual FIT determination is not superior to the incidence in patients undergoing endoscopic surveillance.

### 2.2. Objectives

The main objective of our study is to compare the 10-year CRC incidence between patients undergoing endoscopic surveillance and patients participating in a population CRC screening program based on annual FIT determination. Additionally, we have defined the following as secondary objectives:
-To compare the diagnostic yield for CRC and advanced adenomas detection between both groups at a 3 year interval.-To evaluate the effect of the two surveillance strategies on the following variables: mortality (global and associated with CRC), colonic lesion detection, participation in the surveillance strategy, adverse effects, use of health resources and cost-effectiveness.-To determine the values and preferences of subjects with advanced adenomas resected endoscopically regarding the type of surveillance and the risk of CRC.

### 2.3. Study Design

We designed this study as a randomized, controlled and multicenter clinical trial. We will include patients from the CRC screening programs of Galicia, the Basque Country, the Region of Valencia and Murcia. This study has been registered in ClinicalTrials.gov (ID: NCT04967183).

### 2.4. Inclusion Criteria

Individuals aged from 50 to 65 years with at least one advanced adenoma (tubulovillous or villous histology, high-grade dysplasia or ≥10 mm), and/or at least three non-advanced adenomas, detected and resected completely within the population-based CRC screening program.

### 2.5. Exclusion Criteria

Individuals with (1) personal history of CRC, (2) colonic lesion ≥ 10 mm resected without histological diagnosis, (3) more than 10 adenomas in baseline colonoscopy, (4) serrated polyposis syndrome, (5) two or more first-degree relatives with CRC, (6) hereditary predisposition to CRC, (7) relevant comorbidity with life expectancy inferior to 5 years, (8) colonoscopy with incomplete mucosal examination (no cecal intubation, Boston Score < 6 or <2 in any of the sections), (9) incomplete resection of baseline lesions. (10) piecemeal resection of sessile of flat lesions ≥20 mm and (11) non-acceptance after reading the informed consent.

### 2.6. Study Development: Inclusion

First, patients will have a telephone interview to confirm they meet the inclusion criteria and do not meet any exclusion criteria. Then, we will invite the patients to participate in the study after explaining the trial. In the case of acceptance, we will send them the documentation, including an explanatory brochure, a values and preferences survey, the information sheet and the informed consent that will be returned by postal mail. After receiving the signed informed consent, the patient will be randomly allocated to perform an annual FIT and colonoscopy if fecal hemoglobin concentration is ≥10 µg/g, or to perform endoscopic surveillance. Patients will be also stratified into two groups: ≥5 adenomas or an adenoma ≥20 mm, and the remaining patients. Finally, patients will be informed of the group to which they were assigned by a postal letter, including the recommendation for follow-up. The protocol includes a follow-up period of 10 years.

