### 2.9. Sample Size Calculation

We designed the study on the basis that CRC incidence in the two groups will be 1.24% [16], with a 1:1 ratio between both groups and a non-superiority limit in 1% [17]. Assuming a 0.8 B error and an alpha error of 0.05, 1515 patients should be included in each group. Accounting for an estimated dropout percentage of 20%, it is necessary to recruit 1894 patients in each group, leading to a total of 3788 subjects in the study. This sample size calculation was carried out with the statistical program Ene 3.0.

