### 2.15. Statistical Analysis

The primary analytical approach to the trial will follow the principle of intention to treat (ITT). We will compare the differences for each endpoint between the groups by calculating the incidence, incidence density, risk differences and applying the log-rank test. We will also perform an analysis per protocol to estimate the causal effect that would have been observed if all the people in the intervention arms had met.

For the analysis of the diagnostic yield at three years, we will compare the rates of CRC, adenoma and advanced serrated lesions detection using the risk ratio and relative risk. Logistic regression will be performed to adjust the risk ratio using age, sex, screening program and stratification as confusing variables.

We will also develop a cost–utility Markov model to evaluate the cost-effectiveness of CRC screening. The model will consider different health states based on the usual clinical progression of CRC. We will use the data obtained from this clinical trial, such as transition probabilities, sensitivity, specificity, incidence and mortality rates due to CRC. The EuroQol questionnaire (EQ–5D) [18] will be used to measure the utilities associated with the CRC.

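### The stratum set at allocation is left out of the described primary comparison; using it there is a small, free improvement

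*Protocol article*

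**What the plan says.** Section 2.6 of the protocol article describes random allocation to annual FIT or endoscopic surveillance and continues: "Patients will be also stratified into two groups: ≥5 adenomas or an adenoma ≥20 mm, and the remaining patients". It does not say outright that the randomisation list is stratified, but the position of the sentence makes that the natural reading.

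Section 2.15 sets the general comparison by intention to treat: "We will compare the differences for each endpoint between the groups by calculating the incidence, incidence density, risk differences and applying the log-rank test". The words cover the primary endpoint, and no stratum is mentioned.

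The next paragraph of the same section, on the 3-year diagnostic yield, does bring the factor in: "Logistic regression will be performed to adjust the risk ratio using age, sex, screening program and stratification as confusing variables".

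Section 2.9 sizes the trial without reference to strata: 1.24% CRC incidence in both arms, 1:1 allocation, a limit of 1 percentage point, and "Assuming a 0.8 B error and an alpha error of 0.05, 1515 patients should be included in each group". Dropout of 20% raises this to 1894 per arm.

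**The concern.** A factor used to form the groups at allocation is usually carried into the analysis. Stratified allocation balances the arms on it, and an analysis that leaves it out counts between-stratum variation as noise. Section 2.15 applies the factor to a secondary endpoint and describes the primary comparison without it. Because the article does name the factor in one analysis, its absence from the other is more than general brevity.

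Two things could be at stake. One is precision in a comparison that rests on few events. The other is what a single pooled difference can show. Section 3 cites a cohort in which the benefit of endoscopic surveillance was confined to certain subgroups, adenomas of 20 mm or more among them. If replacing colonoscopy with FIT had a different effect in that stratum, the pooled figure alone would not reveal it.

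**Working it through.** **Inputs from section 2.9.** p = 0.0124 in both arms, margin m = 0.01, 1:1 allocation, alpha 0.05, power 0.80 (worded there as a B error), dropout 20%. Sidedness is not stated; one-sided 0.05 is taken because it reproduces the stated size.

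**Reproducing the plan's figure.**

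n = (z₀.₉₅ + z₀.₈₀)² × 2p(1 − p) / m² = (1.6449 + 0.8416)² × 2 × 0.0124 × 0.9876 / 0.0001 = 6.183 × 244.92 ≈ 1514.3, so 1515 per arm.

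With dropout: 1515 / 0.80 = 1893.75, so 1894. Both match. One-sided 0.025 would give 1923 and does not match.

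**Assumed inputs.** The article gives neither the share f of patients in the ≥5 adenomas or ≥20 mm stratum nor its CRC risk ratio r against the rest. Both are assumed: f from 10% to 50%, r from 1.5 to 4, with the overall rate held at 1.24%.

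**Formulas.**
- Stratum rates: p₀ = p / (1 − f + f·r) and p₁ = r·p₀.
- Unstratified variance: Vu = 2p(1 − p)/n.
- Stratified variance, weights equal to stratum shares: Vs = 2[(1 − f)p₀(1 − p₀) + f·p₁(1 − p₁)]/n.
- If allocation is stratified, Vs is the true sampling variance. Type I error of the unstratified test is then 1 − Φ(1.645·√(Vu/Vs)). Its power is Φ((m − 1.645·√Vu)/√Vs), and the power of the stratified test is Φ(m/√Vs − 1.645).

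**Largest case in the range (f = 20%, r = 4).** p₀ = 0.0124/1.6 = 0.00775 and p₁ = 0.0310.
- Within-stratum term: 0.8 × 0.00775 × 0.99225 + 0.2 × 0.0310 × 0.969 = 0.006152 + 0.006008 = 0.012160.
- Unstratified term: 0.0124 × 0.9876 = 0.012246.
- Ratio Vs/Vu = 0.9929, a reduction of about 0.7%. Required n: 1515 × 0.9929 ≈ 1504.3, so 1505.

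**Selected results.**

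| Share | Risk ratio | Vs/Vu | n per arm | Power, unstratified | Power, stratified | Type I, unstratified |
|---|---|---|---|---|---|---|
| 10% | 1.5 | 0.9997 | 1515 | 80.02% | 80.03% | 0.0500 |
| 20% | 2 | 0.9986 | 1513 | 80.03% | 80.07% | 0.0499 |
| 30% | 3 | 0.9959 | 1509 | 80.07% | 80.16% | 0.0497 |
| 20% | 4 | 0.9929 | 1505 | 80.10% | 80.26% | 0.0494 |
| 50% | 4 | 0.9955 | 1509 | 80.07% | 80.17% | 0.0496 |

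Across the whole range the ratio is 0.993–0.9997 and the power gain is under 0.2 points.

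**Simulation.** There were 400,000 trials per setting, with f of 20% or 40% and r of 2 or 4. Type I error was 5.4–5.5% for both analyses. Power was 79.9–80.1% unstratified and 79.9–80.2% stratified. The excess over 5% is common to both analyses, so the stratum is not its source.

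**Events per stratum.** In the largest case the smaller stratum has 0.2 × 1515 = 303 patients per arm and 303 × 0.031 ≈ 9.4 expected events. Stratum estimates can therefore only be descriptive.

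**The case against.** The best reply is that this is a condensed article. It nowhere says that the primary comparison will be unstratified, and whether a risk difference or log-rank test is stratified is a detail often left to the full protocol or SAP. An unadjusted intention-to-treat risk difference is also a legitimate primary analysis. Both points stand in part: a fuller document may already settle the matter, and nothing in section 2.15 is statistically invalid. What remains is that the article itself names the stratum for one analysis and not for the main one.

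Some stronger readings are tempting, and the documents do not support them.
- A reader might infer that the primary analysis fails to fit the randomisation. Under stratified 1:1 allocation the unstratified comparison stays valid, and section 2.6 does not explicitly say that the list is stratified.
- A reader might take section 3 as showing that the stratum is a strong risk factor for CRC. That passage reports where surveillance benefit appeared, which is effect modification. It covers the size criterion only, says nothing of ≥5 adenomas and gives no risk ratio for this stratum. Section 2.5 also excludes piecemeal resection of sessile or flat lesions of 20 mm or more, so the cohort result does not carry over directly.
- A reader might point to the low event counts, 0.0124 × 1515 = 18.8 or 0.0124 × 1894 = 23.5 per arm. They show that events are rare. They do not measure any loss from omitting the stratum, and the rarity is why adjustment gains so little.
- A reader might expect dropout to unbalance the strata. No dropout difference by stratum is described, and section 2.12 provides for ascertaining CRC and deaths through a pseudo-anonymised identifier when patients change address.

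**Conclusion.** The point holds as a small free improvement and not as an error. The allocation stratum is absent from the described primary comparison and present in a secondary one. With assumed shares of 10–50% and risk ratios of 1.5–4, stratifying lowers the variance by at most about 0.7%, takes the required n per arm from 1515 to between 1505 and 1515, and changes power by under 0.2 points. Leaving the stratum out moves the nominal type I error from 0.05 to no lower than 0.0494, which is slightly conservative. These figures rest on reading section 2.6 as stratified randomisation, on one-sided alpha 0.05, and on the assumed shares and risk ratios. Neither the sample size nor the validity of the conclusion is in question.

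Reporting by stratum matters at least as much as precision. As an assumed illustration, a 3-point excess confined to a stratum with 20% of patients would pool to 0.2 × 3 = 0.6 points, inside the 1-point limit. The documents do not say that this is likely; the example only shows what a pooled figure can conceal.

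**What to change.** In section 2.15, and in the SAP:
- Estimate the 10-year CRC risk difference within each of the two allocation strata and combine the two with Mantel-Haenszel or sample-size weights. Compare the resulting confidence interval with the 1% limit.
- Stratify the log-rank test by the same factor.
- Report each stratum's estimate with its interval, labelled descriptive, since the cohort cited in section 3 suggests that surveillance benefit may differ for adenomas of 20 mm or more.

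If the investigators prefer an unadjusted primary analysis, one sentence saying so would remove the ambiguity, but the stratum estimates should still be reported. Fixing this before outcome data accrue avoids a later choice between two analyses of the primary endpoint. The cost is wording only: the stratum is known at allocation and already enters the 3-year model, and the sample size need not change.

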### 2.7. Study Development: Group I

The CRC screening program will send a kit annually to collect a fecal sample until the surveillance period is completed (10 years) (Figure 1). We will set a cut-off of ≥10 µg hb/g of feces to refer to colonoscopy, which will be performed within the CRC screening program agendas. After performing a work-up colonoscopy, FIT will be sent to the patient:
-After one year if the colonoscopy was incomplete or a lesion requiring endoscopic surveillance was completely resected.-After five years if the colonoscopy evaluated the entire mucosa, was normal or had lesions that do not require endoscopic surveillance (1–2 non-advanced adenomas).

### 2.8. Study Development: Group II

The first surveillance colonoscopy will be performed in a three-year interval (Figure 1). If an advanced adenoma or at least three non-advanced adenomas are detected, colonoscopy will be repeated after three years. On the contrary, if colonoscopy is normal or 1–2 non-advanced adenomas are detected, colonoscopy will be repeated after five years. Surveillance colonoscopy will be considered as the one performed in the interval of 6 months before and 6 months after the established surveillance date. The remaining colonoscopies will be considered unscheduled. Surveillance colonoscopies will not be performed if an unscheduled colonoscopy was performed recently, one of the study endpoints is reached, or there is comorbidity that contraindicates the colonoscopy or the patient rejects.

### 2.9. Sample Size Calculation

We designed the study on the basis that CRC incidence in the two groups will be 1.24% [16], with a 1:1 ratio between both groups and a non-superiority limit in 1% [17]. Assuming a 0.8 B error and an alpha error of 0.05, 1515 patients should be included in each group. Accounting for an estimated dropout percentage of 20%, it is necessary to recruit 1894 patients in each group, leading to a total of 3788 subjects in the study. This sample size calculation was carried out with the statistical program Ene 3.0.

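### Section 2.9 prints power as a beta error of 0.8 and does not say that its alpha of 0.05 is one-sided, the reading on which 1515 per group rests

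*Protocol article*

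**What the plan says.** All the design inputs are in Section 2.9 (Sample Size Calculation) of the protocol article. The assumed event rate is the same in both arms ("CRC incidence in the two groups will be 1.24", in per cent), allocation is equal ("with a 1:1 ratio between both groups"), and the margin is "a non-superiority limit in 1" per cent. The error rates and the result are given in one sentence: "Assuming a 0.8 B error and an alpha error of 0.05, 1515 patients should be included in each group". Allowing for 20% dropout, the article arrives at 1894 recruited per group and 3788 in total.

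Section 2.1 (Hypothesis) is one-directional: incidence under annual FIT is not higher than under endoscopic surveillance. Section 2.15 (Statistical Analysis) makes intention to treat primary and lists incidence, incidence density, risk differences and a log-rank test. Neither section says whether alpha is one-sided or two-sided.

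**The concern.** Two design parameters do not say what the calculation used. First, a beta error of 0.8 is a type II error of 80%, that is 20% power, and it cannot produce the printed sample size. Second, an alpha of 0.05 with no side stated is often taken as two-sided, which for a non-inferiority margin means the upper limit of a 95% interval (one-sided 0.025). The same words could also mean one-sided 0.05, the upper limit of a 90% interval.

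The choice affects the primary conclusion. The two readings differ in power by about 10 percentage points at the planned evaluable number, and some observed differences would pass on one and fail on the other. A reader of a 90% interval also needs to know that the one-sided error is 5%, twice that of a 95% interval.

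**Working it through.** **Inputs (all Section 2.9).** p = 0.0124 in both groups, so the true difference is 0; 1:1 allocation; margin 0.01; dropout 20%. The margin is assumed to be an absolute difference, which the exact match below supports.

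**Formula.** Unpooled normal approximation for non-inferiority of two proportions, per group:

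n = 2p(1 − p)(z_alpha + z_beta)² / margin²

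Here 2p(1 − p) = 2 × 0.0124 × 0.9876 = 0.024492, and dividing by 0.01² gives 244.92.

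**Reproducing the article's figures.** One-sided alpha 0.05, power 0.80:

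- n = 244.92 × (1.6449 + 0.8416)² = 1514.3, rounded up to 1515 (match).
- 1515 / 0.8 = 1893.75, rounded up to 1894 (match).
- 2 × 1894 = 3788 (match).

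**Other readings of the same sentence, per group.**

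| Reading | n per group |
|---|---|
| Beta 0.8 taken literally (power 0.20), one-sided 0.05 | 158.0 → 159 |
| Beta 0.8 taken literally, one-sided 0.025 | 306.3 → 307 |
| Power 0.80, one-sided 0.025 (95% interval) | 1922.4 → 1923 |
| Power 0.90, or two-sided equivalence with beta halved, alpha 0.05 / 0.025 | 2098 / 2574 |
| Farrington–Manning, power 0.80, alpha 0.05 / 0.025 | about 1650 / 2105 |
| Difference test, 1.24% vs 2.24%, power 0.80 (one- or two-sided, with or without continuity correction) | 2114 to 2880 |
| Difference test, 1.24% vs 0.24%, same variants | 908 to 1345 |

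Among these standard variants, only one-sided 0.05 with power 0.80 gives 1515.

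**Power at a fixed n.** Power = Φ(margin / SE − z_alpha), with SE = √(0.024492 / n).

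- n = 1515: SE = 0.004021 and margin / SE = 2.487. One-sided 0.05: Φ(2.487 − 1.645) = 80.0%. One-sided 0.025: Φ(2.487 − 1.960) = 70.1%.
- n = 1894: SE = 0.003596 and margin / SE = 2.781. One-sided 0.05: 87.2%. One-sided 0.025: 79.4%.

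**Size needed for 80% power against a 95% interval.** 1923 evaluable; 1923 / 0.8 = 2403.75, so 2404 recruited per group and 4808 in total.

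**Largest observed excess that still passes with 1515 per group.** With the SE held at equal 1.24% rates, it is 1 − 1.645 × 0.402 = 0.34 points for a 90% interval and 1 − 1.960 × 0.402 = 0.21 points for a 95% interval. If the control arm is at 1.24% and the interval is unpooled, so that the FIT arm's higher rate enters the variance, the limits are about 0.30 and 0.18 points. On either basis there is a band of about 0.12 to 0.13 points in which the two intervals give opposite answers.

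**The case against.** The strongest reply is that nothing has been miscalculated. The figures 1515, 1894 and 3788 are exact, and the size of 1515 itself shows that power 0.80 was meant, so nobody would act on 159. One-sided 0.05 is coherent with a one-directional hypothesis and a single margin, and nothing in the article contradicts it. All of this stands.

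A reader might infer that the trial has only 70% power. The article does not support that. The 70% arises only if the conclusion is read from a two-sided 95% interval, and no such interval is specified for the trial's own analysis. On the design that yields 1515, power is 80%. Nor is 1515 certain to be the final evaluable number: intention to treat is primary, and Section 2.12 plans to ascertain CRC and deaths through an identification number if patients change address. If that recovers outcomes, the evaluable number rises above 1515, up to 79.4% power against a 95% interval with all 1894 followed. Still, the 20% loss is the article's own planning figure, so 1515 is the right basis for a stated power.

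A reader might also fault Section 2.15 for giving no confidence level. An article may leave that to the analysis plan or full protocol, which are not shown, so it is not counted here.

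What the reply does not remove is the wording of Section 2.9 itself. A type II error of 0.8 is false as printed, and the alpha beside it lacks the qualifier on which the sample size depends. An analysis plan may fix the interval level, but it would not correct this published statement.

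**Conclusion.** The point holds as a misstatement of the design parameters, not as an arithmetic error. It should be fixed, but it does not put the sample size in doubt. The beta error of 0.8 should be power 0.80 (beta 0.20), and 1515 per group depends on the alpha of 0.05 being one-sided. If the conclusion is drawn from a two-sided 95% interval instead, power falls from 80.0% to 70.1% at 1515 evaluable per group. These figures assume an absolute margin of 1 percentage point, a true rate of 1.24% in both arms and the normal approximation that reproduces the article's number.

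**What to change.** Preferred: in Section 2.9, replace the error rates with power 0.80 (beta 0.20) and one-sided alpha 0.05, and state that non-inferiority is concluded if the upper limit of the two-sided 90% interval for the risk difference is below 1 percentage point. Read the primary conclusion at that level. No number in the article changes.

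Alternative, if a two-sided 95% interval is intended: keep the recruitment target and state power of about 70% with 1515 evaluable per group, adding that it would be about 79% if all 1894 per group were followed to 10 years. One design figure then becomes less favourable.

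Either way the cost is a change of text, with no extra patients. The choice should be made before outcome data are seen.
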